#### Data collection of quantitative study

The data collection started in January 2020. Due to the pandemic, the rehabilitation centers did not receive any patients from mid-March until about mid-May. To increase the number of recruited patients, two more rehabilitation centers joined the project in August 2020 (initially there were only three centers). The recruitment of the patients is planned to finish in October 2021. In total, the data collection includes four measurement occasions. The baseline measurement takes place at the rehabilitation center before the start of the intervention, the first follow-up measurement 13 weeks after the baseline, the second follow-up 26 weeks after the baseline, and the third follow-up 43 weeks after the baseline (see Fig. 2). The first three measurement occasions represent the development of the outcome variables, approximately, before, during and at the end of the intervention. Due to the limited duration of the study, the last follow-up measurement is intended to illustrate the sustainability of developments over the next 4 months. For the measurements 2–4, the questionnaires are directly sent to the patients, in accordance to their preference via post or e-mail. A reminder is sent in case the patients have not returned the questionnaires after 2 weeks.

**Fig. 2 Fig2:**
[figure not shown]
Design of the quantitative study part

#### Measures

The attendance, work ability, subjective health, and motivation will be measured to compare the development of the three groups (i.e., web-based aftercare, traditional face-to-face aftercare, control group). While the work ability, subjective health, and motivation are assessed at every measurement occasion, the attendance is not assessed at the first measurement occasion. Furthermore, attendance and motivation are only assessed in the web-based aftercare and the traditional face-to-face aftercare groups.

#### Attendance

This part of the questionnaire was developed for this study. Patients in the traditional face-to-face aftercare group and the web-based aftercare group are asked (a) how often they participated in their program and (b) how many minutes within a week on average they trained with their program. Furthermore, patients of all three groups will be asked about their average weekly participation in other sport activities.

#### Work ability

The German version of the Work Ability Index (WAI) as an internationally established instrument is used to measure the work ability of the patients [26]. The WAI consists of ten questions with categorical and continuous response formats, resulting in a score from a minimum of 7 to a maximum of 49. This score indicates the current assessment of one’s own work ability to deal with the work demands. The WAI has been shown to have an acceptable Cronbach᾽s α = 0.78 [27] and to predict an early work termination and long-term work disability [18, 19].

#### Subjective health

The German version of the SF-12 is used to measure the subjective health [28]. The SF-12 consists of 12 items with dichotomous and continuous response formats, which comprise the two dimensions physical and mental health. Studies have shown good Cronbach᾽s α = 0.83 for physical health and α = 0.87 for mental health [28]. Moreover, the SF-12 can be used independent of the current health status, and the questions have been deemed as understandable and relevant [29].

#### Motivation

The Behavioural Regulation Exercise Questionnaire-2 [BREQ-2 [30]], translated into German, is used to measure motivation. The questionnaire consists of 19 items with a five-point Likert scale, measuring five dimensions of motivation: intrinsic motivation, identified regulation, introjected regulation, extrinsic motivation, and amotivation. The reliability has been shown to range from acceptable to good for the different dimensions: intrinsic motivation (*α* = 0.88), identified regulation (*α* = 0.83), introjected regulation (*α* = 0.77), extrinsic motivation (*α* = 0.77), and amotivation [*α* = 0.60; 30]. In addition, the subscales show inter-correlations in line with theoretical considerations, and more autonomous types of motivation are associated with a higher probability of health behaviours [31].

#### Data analysis of quantitative data

Data are entered by research assistants and checked for accuracy by an independent research assistant. All personal information is pseudo-anonymized. Missing data are treated using either the multiple imputation or the full-information maximum likelihood approach. A first analysis will include all patients who intended to participate in the interventions and a second study will include only those patients who actually completed the interventions. A multivariate analysis of variance with repeated measurements will be used to analyze the data. Additionally, the development of work ability and subjective health will be analyzed by latent growth curve models [32]. These models allow the analysis of linear and nonlinear developments over time. A mediation analysis will be conducted to test whether motivation mediates the effects of the intervention on the attendance rate. The effects of age and gender will be controlled.

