**Methods:**

The goal is to recruit up to 1150 patients at baseline in five rehabilitation centers across Germany. For ethical reasons, partially randomized experimental study design is used to quantitatively assess the effectiveness of web-based aftercare programs. All patients are offered the traditional face-to-face aftercare treatment (IRENA). When patients deny to participate in traditional face-to-face aftercare, they are randomly distributed into either web-based aftercare (digIRENA) or a control group. In all three groups, the SF-12, which measures subjective health, and the WAI, which measures working ability, will be used at baseline, 13 weeks, 26 weeks and 43 weeks after the patients have left the rehabilitation center. BREQ-2, which measures motivation, is used only in the traditional aftercare group and the web-based aftercare group. A multivariate analysis of variance with repeated measurement and latent growth curve models will be used to compare the development of the variables in the three groups. For the qualitative part of the study, interviews with patients and therapists will be conducted to shed light on the applicability, acceptance, and usability of web-based aftercare programs.

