#### Intervention

In this study, two rehabilitation aftercare programs are implemented: the traditional face-to-face aftercare program (IRENA; Intensified Rehabilitation Aftercare) and the web-based aftercare program (digIRENA; digitized Intensified Rehabilitation Aftercare). Both aftercare programs consist of 24 sessions and are tailored to the orthopaedic conditions of the rehabilitants [24]. The program has to be conducted by a qualified physiotherapist who selects the contents of the aftercare program. In the web-based aftercare program, the subjects receive a comparable individualized program with the same number of sessions as the traditional face-to-face IRENA. The web-based program is supervised by an external team of physiotherapists, employed by the provider of the web-based platform. Moreover, the web-based platform provides tools such as relaxation exercises or cooking recipes equivalent to the multimodal approach of a traditional face-to-face aftercare program. In both programs, if patients do not attend a session for at least six subsequent weeks, they are considered dropouts. If inactive, the intervention provider in the web-based aftercare program can encourage the patient to remain in the intervention. Patients in both aftercare groups are continuously supervised by qualified therapists during the interventions. In case of possible harm from the intervention, patients can be referred to appropriate treatment. The participants in the control group receive neither IRENA nor digIRENA. However, they have the possibility to organize their own rehabilitation activities. Finally, all patients can receive additional therapies depending on their health status.

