#### Sampling and participants

Patients with orthopedic complaints who have applied for and been approved for rehabilitation on the prescription of a primary care physician are recruited from five rehabilitation centers throughout Germany. The inclusion criteria are that patients are at least 18 years old, have a basic knowledge of the German language, and their primary diagnosis concerns an orthopaedic problem. Furthermore, only patients who are insured with the public pension insurance Knappschaft Bahn See can participate in the study, as the included rehabilitation centres belong to Knappschaft Bahn See. When patients are informed about the possibility to take part in an aftercare program during their stay, they are also asked to participate in the study. In case they give their consent, they are assigned to three groups: (1) traditional face-to-face aftercare program (IRENA), (2) web-based aftercare program (digIRENA), or a control group. For ethical reasons, a partial randomized controlled trial was used. All patients are first asked whether they want to take part in the traditional aftercare program (IRENA). Only if they deny, they are randomly assigned to the web-based aftercare program or the control group. This means that the IRENA condition was offered preferentially and the randomization referred only to the digIRENA and control condition. Sealed envelops are used for the randomization and patients only know their group after opening the envelop. The envelops are distributed with the goal to obtain a ratio of 1:1 between the two groups. Due to nature of the study neither participants nor staff can be blinded to allocation. As an incentive to take part in the study, all patients who complete the study with all measurement occasions receive a 50 Euro Amazon voucher.

Because only a small number of studies exists in relation to web-based aftercare interventions, we chose to take a conservative approach in the power analysis with a small estimated effect size [8]. Conservatively estimating the effect size by Cohen’s *f* = .15, *α* = .05, 1-*β* = .80, with three groups, a correlation among repeated measures of *r* = .30 and a design with three repeated measurement occasions, on average, using an ANOVA with repeated measures (within-between interaction), the calculated total sample size is 573 participants, nearly equally distributed over three groups. Since we expect a dropout rate of about 50% [25], the plan is to recruit 1150 patients.

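### Neither analysis set is defined by allocated group, and the completer analysis leaves the randomised digIRENA versus control contrast without a valid control group

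*Protocol article*

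**What the plan says.** In the protocol article, the section on data analysis of quantitative data fixes two analysis sets. On the first: "A first analysis will include all patients who intended to participate in the interventions". On the other: "a second study will include only those patients who actually completed the interventions". The section does not mention allocated group, does not say where control patients belong in either set, and names neither analysis as the main one.

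The Intervention section describes two programmes, IRENA and digIRENA, of 24 sessions each. It says of the third group: "The participants in the control group receive neither IRENA nor digIRENA". Its attendance rule, that "if patients do not attend a session for at least six subsequent weeks, they are considered dropouts", is stated for the two programmes only.

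Under Sampling and participants, patients who decline IRENA are randomised: "the randomization referred only to the digIRENA and control condition". The allocation aim is: "The envelops are distributed with the goal to obtain a ratio of 1:1 between the two groups". Patients learn their group only on opening the envelope. According to the Methods part of the abstract, the planned models "will be used to compare the development of the variables in the three groups", so the control group is meant to be part of the comparison.

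**The concern.** The trial has one randomised contrast, digIRENA against control. The Discussion relies on the partially randomised design for strong conclusions about effectiveness, and that reliance is justified only if these two groups are compared as allocated.

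An analysis set defined by completing a programme selects patients in the digIRENA arm after randomisation. Nothing matching can be applied to the control arm. Any difference in prognosis between those who finish and those who do not is then read as a programme effect. Motivation is one plausible driver of completion: the Background links autonomous motivation to keeping up a healthier lifestyle. The article measures motivation only in the two aftercare groups, so the comparison with control cannot be adjusted for it.

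The first set carries a smaller risk. Taken literally, control patients, or digIRENA patients who never start, could be left out.

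**Working it through.** **Step 1: apply each definition to each group.**

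| Group | Intended to take part | Completed the intervention |
|---|---|---|
| IRENA (chosen) | yes | can be judged |
| digIRENA (randomised) | yes, though a patient who never starts is unclear | can be judged, though completion is not defined: 24 sessions, or not meeting the six-week rule |
| Control (randomised) | unclear: declined IRENA, accepted randomisation, offered no programme | cannot apply |

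The last cell allows two readings of the completer analysis. Either controls are excluded and there is no control comparison, or all controls stay in and face a selected part of the digIRENA arm. Neither is the randomised contrast.

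**Step 2: what the plan's 50% stands for.** The sample size section says "Since we expect a dropout rate of about 50" per cent and plans to recruit 1150. The step reproduces: 573 / (1 − 0.50) = 1146, rounded up to 1150. It is an allowance between recruited and analysed patients over all three groups. The article gives no figure for programme non-completion, so completion has to be varied as an assumption.

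**Step 3: size of the bias if all controls are kept.** Let p be the share of the digIRENA arm that completes. Let delta be the difference in change over time, in SD, between would-be completers and would-be non-completers if neither were treated. Delta must refer to change, because the sample size is based on the group-by-time interaction and a stable difference in level does not enter that test.

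- Expected change in completers with no programme effect: mu_N + delta, where mu_N is the mean change of non-completers.
- Expected change in unselected controls: mu_N + p × delta.
- Spurious difference: (1 − p) × delta.

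| Completion p (assumed) | delta = 0.3 | delta = 0.5 |
|---|---|---|
| 75% | 0.25 × 0.3 = 0.075 | 0.25 × 0.5 = 0.125 |
| 50% | 0.50 × 0.3 = 0.15 | 0.50 × 0.5 = 0.25 |

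With delta = 0 there is no bias. With delta negative, the sign reverses.

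**Step 4: check with a different model.** Suppose completion follows a normal propensity that has correlation rho with untreated change. The bias is rho × phi(c) / p, where phi is the standard normal density and c the cut-off that gives share p. At p = 0.50, c = 0 and phi(c) = 0.399. The bias is 0.08, 0.16 and 0.24 SD for rho = 0.1, 0.2 and 0.3. At p = 0.75 it is 0.04 to 0.13 SD over the same range of rho. A simulation at 50% completion with a true effect of zero gave the same biases. For 191 completers against 191 controls (573 / 3 each), a plain two-sided comparison of means was falsely positive in 12%, 35% and 65% of runs, against a nominal 5%. These rates show how the bias acts; they do not apply exactly to the planned repeated-measures model. Rho, like delta, is assumed.

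**The case against.** Several points on the other side are sound.

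- **The first set.** A reader might infer that both analyses lack a valid control group and that randomisation is lost in both. The article does not support this. The pairing of intended with completed reads naturally as a condensed intention-to-treat and per-protocol pair. The abstract, the opening of the quantitative study section and the Measures section all keep the control group in the comparison. Controls also agreed to be randomised before knowing their group. What stands is that the wording is loose.
- **The 50%.** A reader might infer that half the digIRENA arm will fail to complete. The article does not say so (step 2 of the working).
- **Direction.** A reader might infer that the completer contrast must favour digIRENA. The Background names lack of time after returning to work as a main reason for not attending aftercare. Non-completers could therefore include patients whose work ability is doing better, which would bias the contrast against digIRENA.
- **Place of the completer analysis.** It is the second of two, and a per-protocol set beside an intention-to-treat set is common. An article may leave its details to a fuller document. That excuses the missing definition of completion. It does not excuse the stated rule, which cannot be applied to one of the two randomised groups.
- **Missing-data methods.** Multiple imputation or full-information maximum likelihood addresses outcomes that were not observed. It does not undo the deliberate exclusion of non-completers.

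**Conclusion.** The point holds in this form. Neither set is defined by allocation. For the first set this is an ambiguity to be closed, not a demonstrated loss of the comparator. For the second it is a substantive fault: followed as written, the analysis has no control group or breaks the trial's only randomised contrast.

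The completer contrast is open to bias if completion is related to change in outcome; how much, and in which direction, cannot be learned from the article. The illustrative range of about 0.08 to 0.25 SD rests on assumed completion of 75% to 50% and an assumed untreated difference in change of 0.3 to 0.5 SD. Comparisons with IRENA are non-randomised under any definition, because those patients choose their programme.

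**What to change.** 1. **Main analysis.** Compare digIRENA with control in all randomised patients, each in the group drawn from the envelope, including those who never start and those who meet the six-week rule. Show IRENA choosers as a separate, non-randomised group.
2. **Effect of taking part.** Replace the completer-versus-control comparison with a complier-average effect of digIRENA, using allocation as the instrument. Controls receive no digIRENA, so non-adherence is one-sided. Define a complier by any uptake. This assumes that allocation has no effect on patients who would never take up the programme, which deserves a comment because controls may organise their own activities. A definition by a minimum number of sessions needs the further assumption that fewer sessions have no effect.
3. **Completers.** State what counts as completion and report completers only as descriptive or supportive.

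The cost is wording and one extra model. The article already sends follow-up questionnaires directly to patients and does not make this depend on attendance, so no new data are required.

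The price in precision can be sketched for n patients per arm, equal variances and uptake equal to completion p. The naive standard error is proportional to sqrt(1/(pn) + 1/n), and the complier-average one approximately to sqrt(2/n) / p. Their ratio is 1.886 / 1.528 = 1.23 at p = 0.75 and 2.828 / 1.732 = 1.63 at p = 0.50. If uptake exceeds completion, the ratio is smaller.

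### For the randomised digIRENA–control contrast the repeated-measures MANOVA works on change from baseline; adjusting for baseline would cut single-visit variance by 35% at the plan's own r = .30

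*Protocol article*

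**What the plan says.** Under the heading on the analysis of quantitative data, the first method named is: "A multivariate analysis of variance with repeated measurements will be used to analyze the data". Latent growth curve models for work ability and subjective health are added to it, and age and gender are the only variables to be controlled. The abstract lists the two methods side by side. On incomplete data the same section says: "Missing data are treated using either the multiple imputation or the full-information maximum likelihood approach".

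The section on sampling and participants shows which effect is tested: "using an ANOVA with repeated measures (within-between interaction), the calculated total sample size is 573 participants". The inputs include "a correlation among repeated measures of *r* = .30 and a design with three repeated measurement occasions, on average". It then says: "Since we expect a dropout rate of about 50% [25], the plan is to recruit 1150 patients".

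The data collection section says: "In total, the data collection includes four measurement occasions". These are baseline and weeks 13, 26 and 43, so baseline is part of the repeated outcome. Only digIRENA and control are allocated at random, in a 1:1 ratio, among patients who decline IRENA. IRENA patients choose their group.

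**The concern.** A group-by-time test uses only within-patient contrasts. With baseline as one of the occasions, the digIRENA–control part of that test compares how far the two groups moved from their starting values. Randomisation already makes the expected baseline values equal, so the difference at follow-up is unbiased without subtracting anything. Subtracting a baseline that correlates only .30 with follow-up removes little between-patient variation and adds the full measurement noise of the baseline. Using baseline as a covariate removes just the predictable part.

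What is at stake is precision in the one comparison that can carry a causal claim about web-based aftercare. The discussion section counts the ability to find small effects as a strength, and the pandemic interrupted recruitment. The baseline value is already collected, so the precision is available without extra data.

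**Working it through.** **Inputs.** Correlation between occasions r = .30, three groups, analysed total 573, dropout about 50% and target 1150 (sampling section); four occasions including baseline (data collection section). Equal correlations and equal variances across occasions are assumed, in line with a single r. Variances are in units of the outcome variance σ².

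**The plan's own figures.**
- Dropout step: 573 / (1 − 0.50) = 1146, about 1150. This reproduces.
- The 573 does not. With f = .15, three groups and three occasions, the usual noncentral F calculation (λ = f²·N·3/(1 − r), 4 and 2(N − 3) degrees of freedom) gives N = 127, or 129 in equal groups. The nearest variant tried at three occasions, λ = f²·N without r, gives 533. This is a separate matter. The variance comparison below needs only r; 573 is used only to express it as a detectable difference.

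**One follow-up, r = .30.**
- Change from baseline: 2(1 − r) = 2 × 0.70 = 1.40.
- Baseline as covariate: 1 − r² = 1 − 0.09 = 0.91.
- Ratio 0.91/1.40 = 0.65, so the variance is 35% lower. The reverse, 1.40/0.91 = 1.54, is worth 54% more patients. A simulation with 190 per arm gave 35–36%.

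**Mean of three follow-ups, r = .30.**
- Variance of the mean: (1 + 2 × 0.30)/3 = 0.533.
- Change from baseline: 0.533 + 1 − 2 × 0.30 = 0.933.
- Baseline as covariate: 0.533 − 0.09 = 0.443.
- Reduction 1 − 0.443/0.933 = 52.5%.

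**Link to the omnibus test over four occasions.** Take a difference d that is zero at baseline and constant at all three follow-ups. Its squared deviations from its own mean sum to (0.75d)² + 3 × (0.25d)² = 0.75d². Divided by 1 − r = 0.70 this is 1.071d², which equals d²/0.933. So for a sustained effect the interaction test carries exactly the information of the mean change. With baseline as covariate the figure is d²/0.443 = 2.256d², a ratio of 2.1. If the effect is confined to one visit, the omnibus gain is much smaller. The sum is again 0.75d², hence 1.071d². The adjusted figure is (1/0.70) × (1 − 0.21/1.33) = 1.203d², a ratio of 1.12. Here 0.21 = r − r² is the covariance between follow-ups given baseline, and 1.33 = 0.70 + 3 × 0.21.

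**Other correlations (assumed).** The single-visit reduction is (1 − r)/2, positive for every r below 1.

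| r | change | adjusted | reduction, one visit | reduction, mean of three |
|---|---|---|---|---|
| .3 | 1.40 | 0.91 | 35% | 52.5% |
| .5 | 1.00 | 0.75 | 25% | 37.5% |
| .7 | 0.60 | 0.51 | 15% | 22.5% |
| .8 | 0.40 | 0.36 | 10% | 15% |

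**Detectable difference.** 573/3 = 191 per arm. For 80% power at two-sided .05 and one visit: 2.80 × √(2/191) = 0.287 SD, multiplied by √1.40 for change (0.34 SD) or √0.91 for adjustment (0.27 SD). The adjusted analysis behaves like a change analysis with 191 × 1.54 = 294 per arm.

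**The case against.** **The planned analysis is valid and matches the stated aim.** This stands. The interaction test suits the wish to compare development over time and agrees with the test used for the sample size. For digIRENA against control, though, both analyses estimate the same treatment difference, so the more precise one loses nothing.

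**The size is conditional.** This also stands. The 35% is for one visit and one planning value of r. The omnibus test is not a single-visit change score, and its gain ranges from 12% to about double the information according to the shape of the effect. Nor is the loss shown to endanger the power target: the usual formula with the plan's inputs puts power at 573 above 99.9%.

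**A likelihood-based longitudinal model is already planned.** The growth curve models are close relatives of the proposed model, so the change is partly one of rank. But they are introduced as additional to the MANOVA, and the outcome's baseline value is not named as a covariate.

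**IRENA does not fit the argument.** Correct. Its patients select themselves, so baseline levels may differ. Change and baseline-adjusted analyses then answer different questions, and neither is simply the more precise version of the other.

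**Stronger readings the text does not support.** A reader might infer that, with about half the patients dropping out, the MANOVA would delete incomplete cases and rest on completers. No listwise deletion is planned. Multiple imputation is allowed and works with a MANOVA; full-information maximum likelihood does not apply to a classical MANOVA but fits the growth models. Both keep partial responders. A reader might also see errors in the absence of centre from the model or in doubling the sample for dropout. The article does not say that allocation was stratified by centre, a condensed article may leave that covariate to the full plan, and the inflation is conservative.

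**Conclusion.** The point holds as a gain in efficiency that should be taken, not as a flaw that invalidates the plan. For the randomised contrast, treating baseline as an outcome costs precision that adjustment would recover: 35% of the variance at one follow-up and about 53% for the mean of three at r = .30, or 25% to 10% at one follow-up if r is .5 to .8. The figures assume equal correlations and variances across occasions and apply to digIRENA against control only. The 0.34 and 0.27 SD also depend on 191 per arm, from a total that does not reproduce. The gain comes from conditioning on baseline; a mixed model that kept baseline as a free outcome would not bring it.

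**What to change.** - For digIRENA against control, make the main analysis of WAI, SF-12 physical and SF-12 mental a likelihood-based repeated-measures model of weeks 13, 26 and 43, with group by visit, baseline value by visit, age and gender. Include every randomised patient with at least one follow-up value.
- Report comparisons with IRENA separately and label them non-randomised.
- Keep the latent growth models, fitted by full-information maximum likelihood, as secondary.
- If a MANOVA is retained, pair it with multiple imputation, and say which missing-data method serves which model.

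The cost is wording in the analysis plan and standard software; no new data are needed. The downside is that one omnibus three-group p-value gives way to outcome-specific estimates.

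### The planned mediation of the intervention's effect on attendance can only compare IRENA with digIRENA, which is not a randomised contrast, and motivation has no randomised comparison because controls do not receive BREQ-2

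*Protocol article*

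**What the plan says.** Allocation is described under Sampling and participants. Every patient is first offered IRENA. "Only if they deny, they are randomly assigned to the web-based aftercare program or the control group". The article adds that "the IRENA condition was offered preferentially and the randomization referred only to the digIRENA and control condition".

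The Measures section opens by listing attendance, work ability, subjective health and motivation as variables that "will be measured to compare the development of the three groups". The same paragraph then says that "attendance and motivation are only assessed in the web-based aftercare and the traditional face-to-face aftercare groups". The abstract agrees on motivation: "BREQ-2, which measures motivation, is used only in the traditional aftercare group and the web-based aftercare group". The Attendance section agrees on attendance: "Patients in the traditional face-to-face aftercare group and the web-based aftercare group are asked (a) how often they participated in their program". The only activity item put to everyone concerns something else: "patients of all three groups will be asked about their average weekly participation in other sport activities".

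The section on analysis of the quantitative data then plans the mediation: "A mediation analysis will be conducted to test whether motivation mediates the effects of the intervention on the attendance rate". It names age and gender as the variables to be controlled. It does not say which groups are compared or that the comparison is non-randomised.

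**The concern.** A mediation analysis of an intervention effect needs an exposure contrast, a mediator and an outcome in the same groups. Here the exposure contrast that randomisation protects and the groups in which mediator and outcome are observed do not coincide. The sentence on mediation reads as an analysis of how the intervention works, but the data can only show how people who took up face-to-face aftercare differ from people who turned it down and were then given the web-based programme.

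The Discussion lists attendance (1a) and motivation (1d) among the efficacy purposes and says that the partially randomised design supports strong conclusions about effectiveness. For 1a, 1d and the mediation, randomisation contributes nothing. A reader could take an indirect effect as evidence about the mechanism of digIRENA when it may be a selection effect.

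**Working it through.** The point is structural, so the main step is to set the sections side by side.

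| Group | How patients enter | Randomised contrast | Motivation (BREQ-2) | Programme attendance |
|---|---|---|---|---|
| IRENA | accept the offer | no | yes | yes |
| digIRENA | decline, then randomised | yes, against control | yes | yes |
| Control | decline, then randomised | yes, against digIRENA | no | no (no programme) |

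- Randomised pair: {digIRENA, control}.
- Pair with both mediator and outcome: {IRENA, digIRENA}.
- Overlap: digIRENA alone. One group is not a contrast, so the mediation has zero randomised contrasts.

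What remains is IRENA against digIRENA, that is, acceptors against randomised decliners. If acceptance is related to motivation, the exposure-to-mediator path is confounded. If it is related to attendance, the exposure-to-outcome path is confounded. The article's Background names lack of time and distance as reasons for not taking part, and these could affect attendance as well. Age and gender do not stand in for any of this.

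*How much selection matters (illustration; the SD differences are assumed and do not come from the article).* Planned analysed size is 573 in three nearly equal groups: 573 / 3 = 191 per group. For a two-sided 5% comparison of two means with no true effect and a residual selection difference of d SD, let s = d / √(2/191), where √(2/191) = 0.1023. The probability of a significant result is 1 − Φ(1.96 − s) + Φ(−1.96 − s):

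- d = 0: 5%
- d = 0.1: s = 0.98, about 16%
- d = 0.2: s = 1.95, about 50%
- d = 0.3: s = 2.93, about 83%

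This concerns a simple group difference in motivation or attendance, not the indirect effect itself.

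*Size of a randomised comparison of motivation.* With BREQ-2 in both randomised groups: 2 × 191 = 382 patients at planned sizes. This is an upper bound, because controls already enrolled have no baseline BREQ-2.

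*The plan's own figure.* The 573 is used here only as the planned analysed number. The step to recruitment is consistent: 573 / (1 − 0.5) = 1146, close to the stated 1150. The 573 itself does not follow from the stated inputs: with λ = f²·N·m/(1 − r), f = 0.15, m = 3 occasions, r = 0.30 and three groups, 80% power is reached at N = 129 (in multiples of three). That is a separate matter, and the structural conclusion does not depend on it.

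**The case against.** The best defence is that the article discloses, in the abstract and in Measures, who receives which instrument, and that controls have no programme to attend. Any question about programme attendance is then necessarily IRENA against digIRENA. This stands for attendance: its absence in controls is no measurement failure. It does not cover BREQ-2, whose omission in controls was a design decision that no analysis plan can undo. It also does not make IRENA against digIRENA a randomised comparison.

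It can also be said that this is one sentence about a supplementary analysis. That is fair as to weight: the digIRENA versus control comparisons of WAI and SF-12 are untouched.

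Several stronger readings are tempting but not supported:

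- *Attendance may simply drive motivation, because both are recorded together.* Motivation is assessed at every occasion and attendance at every occasion after the first, so week-13 motivation can be related to attendance reported at week 26. The article does not say which occasions enter the model.
- *Both groups in the mediation are self-selected.* Patients in digIRENA are randomised among decliners. The selection lies in the split between acceptors and decliners.
- *Motivation is known to determine the choice of IRENA.* This is plausible, but it is an assumption. The article's stated reasons for non-participation are time and distance.
- *Giving BREQ-2 to controls would make the mediation causal.* It would randomise the exposure only. The path from mediator to outcome stays observational.

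**Conclusion.** The concern holds in this form: the mediation and the attendance comparison are non-randomised comparisons of IRENA with digIRENA, and objective 1d has no randomised comparison because controls do not receive BREQ-2. This follows directly from the article's own sections. The further step, that the contrast is biased, rests on the plausible but undocumented assumption that acceptance of face-to-face aftercare is related to motivation and attendance beyond age and gender. The size of any bias is unknown. On the assumed range of 0.1 to 0.3 SD, the chance of a spurious group difference runs from about 16% to about 83%.

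The opening of the Measures section, which promises a three-group comparison, conflicts with the two-group restriction later in the same paragraph. This is a wording fault, to be reconciled. The point limits what may be concluded about attendance, motivation and mechanism. It does not weaken the randomised comparisons of work ability and subjective health.

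**What to change.** 1. *Relabel and strengthen the planned analysis.* State that the mediation and the attendance comparison are non-randomised analyses of IRENA against digIRENA. Adjust for baseline BREQ-2, WAI and SF-12, which are already collected in both groups, as well as age and gender. Take motivation from an occasion before the period that the attendance measure covers. Report the result as association, not as an effect of the intervention. Reconcile the opening of Measures with its two-group restriction, and make clear in the Discussion that randomisation does not support conclusions on 1a or on the mediation. This needs no new data. Its limit is that the adjustment is only partial.

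2. *Add BREQ-2 for controls from now on.* Include it with the questionnaires that they already receive, and compare motivation between digIRENA and control as randomised. That controls can answer it is inferred from its description as an exercise-regulation questionnaire and from the fact that they may organise their own activities; this should be confirmed. Any mediation in these two groups, on an outcome measured in both such as WAI or SF-12, should be called exploratory.

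The cost of the second step is 19 extra items for control patients and an amendment. Data collection began in January 2020 and recruitment was planned to end in October 2021, so controls already enrolled would lack baseline BREQ-2, and the comparison would include fewer than the roughly 382 randomised patients at planned sizes. If recruitment is too far advanced for this, the first step alone is the minimum, and objective 1d should be stated as having no randomised comparison.
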